# Comparative effects of nebivolol and carvedilol on left ventricular diastolic function in older heart failure patients with preserved ejection fraction: study protocol for a randomized controlled trial

**DOI:** 10.1186/s13063-016-1656-y

**Published:** 2016-11-03

**Keywords:** Nebivolol, Carvedilol, Heart failure

## Abstract

**Background:**

Heart failure (HF) is a common and disabling condition in older people. Randomized clinical trials and meta-analyses have clearly demonstrated that the long-term use of β-Blockers improves the outcome of patients with HF. However, limited data are available on the treatment of older HF patients with preserved ejection fraction (EF). No study has specifically compared the relative effectiveness of carvedilol and nebivolol in treating HF in older patients with preserved EF.

**Method/design:**

This trial is a prospective, randomized, open-label, single-centre, active controlled study designed to investigate the effects of nebivolol and carvedilol on diastolic function of the left ventricle (LV) in older HF patients with preserved EF.

We will test the hypothesis that nebivolol improves LV diastolic function to a greater extent than carvedilol in patients over 70 years of age. The study population includes 62 older patients newly diagnosed with HF. Patients will be included in the study if they have a LVEF ≥40 %, New York Heart Association (NYHA) functional classes I, II or III status, and have been clinically stable without hospital admission for HF in the preceding 3 months. Eligible patients will be randomly assigned, in a 1:1 ratio, to receive a loading and maintenance dose of either nebivolol or carvedilol. Echocardiographic evaluations will be performed at baseline, 6, and 12 months after therapy. Clinical assessment and laboratory tests are to be performed at fixed times.

**Discussion:**

This trial is a single-center study that aims to evaluate the impact of nebivolol on LV diastolic function. The results of the study will provide information about the optimal choice of a β-Blocker in the management of patients after diagnosis of HF with preserved EF. The results will be available by 2017.

**Trial registration:**

ClinicalTrials.gov Identifier: NCT02619526, registered on 25 November 2015.

**Electronic supplementary material:**

The online version of this article (doi:10.1186/s13063-016-1656-y) contains supplementary material, which is available to authorized users.

## Background

Heart failure (HF) is a common disease in older people, and has a pronounced negative impact on quality of life and functional status [1, 2]. The use of β-Blockers has been proven to improve left ventricular (LV) systolic function and the prognoses of patients with HF in randomized controlled trials [3–6]. Thus, β-Blockers are considered a cornerstone in the pharmacological treatment of HF. However, data have shown that the median age of presentation of new HF cases is older than 75 years [2, 7, 8]. For patients with HF aged 70 and over the evidence for the efficacy of β-Blockers is limited. Only the SENIORS (Study of Effects of Nebivolol Intervention on Outcomes and Rehospitalization in Seniors With Heart Failure) trial has investigated the effect of nebivolol in HF patients over the age of 70 years. Those results demonstrated a significant reduction in the risk of death and cardiovascular-related hospitalization in patients given β-Blockers as compared with a placebo [6]. In a subanalysis of the SENIORS trial, the effect of nebivolol in older patients with HF was shown to be similar in those with preserved and impaired ejection fraction (EF) [9].

However, no study has specifically compared the relative effectiveness of nebivolol and carvedilol in treating HF in older patients with preserved LV function. This open-label study will compare the effects of long-term treatment with nebivolol versus carvedilol on LV diastolic function in older patients with HF.

## Trial objectives

The primary question to be tested is whether nebivolol improves LV diastolic function as measured by echocardiography in older patients with preserved EF during a follow-up period of 1 year, compared with the usual dose of carvedilol in the control group.

The secondary objective of the study is to assess the effect of the two β-Blockers on clinical outcomes. Clinical events are defined as symptom severity (New York Heart Association (NYHA) classification) and hospitalization due to HF.

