### Outcome measurements

The primary efficacy variables are mitral inflow velocities (E and A waves), deceleration time of the E wave (DT), isovolumetric relaxation time (IVRT), mitral annular velocities (early diastolic velocity of mitral annulus (Ea) and late diastolic velocity of mitral annulus (Aa) waves), left atrial (LA) volume, and LA strain (global systolic and diastolic LA strain), which will be measured via echocardiographic evaluation after 12 months of treatment. Mitral E/A and E/Ea ratios will be calculated. Parameters from Doppler analysis, M-mode echocardiography, and 2D-transthoracic echocardiography will be used. All echocardiographic images will be interpreted by an observer who is blinded to clinical data.

Secondary outcomes include occurrence of clinical events. Symptom severity (NYHA classification) and hospitalization will be evaluated at baseline and at maintenance follow-up visits. Vital signs, including heart rate and blood pressure, will be measured at every visit. Any complications, discontinuations, and deaths occurring during the study period will be noted. Each patient’s medical history and the results of a clinical examination will be recorded at baseline by the attending physician.

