### Follow-up protocol

On achievement of the target dose or the maximum tolerable dose, patients will be followed up clinically every month for the first 3 months, then every 3 months until the end of the study at 12 months. At each visit, patients will undergo a complete physical examination, medical history-taking, and assessment of drug compliance. Investigators will evaluate all clinical and laboratory adverse events at each visit. NYHA functional class and predefined clinical events will be recorded at each clinical visit. Echocardiographic examinations will be performed at 6 and 12 months after discharge.

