### Statistical analyses

The intent-to-treat (ITT) analysis set will be used for efficacy analyses. All patients who have begun treatment will be included irrespective of their protocol adherence and continued participation in the study. Patients will be analyzed according to their randomized study medication irrespective of whether a SAE occurred before or following discontinuation of study medication. For baseline characteristics, continuous variables will be assessed using the Student’s *t* test and discrete variables will be compared using the chi-square test. The primary outcome will be compared using two-sample *t* tests. The two-sided null hypothesis for the primary outcome measure states that nebivolol and carvedilol lead to the same change in ventricular diastolic function during the 12 months after diagnosis. This null hypothesis will be tested by regression analysis adjusted for baseline values. Assessments for other echocardiographic indices will be compared between treatment groups after 12 months of follow-up using two-sample *t* tests. Analyses of changes will be performed using data from all patients for whom baseline and 12-month follow-up data are available. Event-free cumulative survival rates will be plotted using the Kaplan-Meier method and comparisons will be made between patients given nebivolol and carvedilol using the log-rank test. A Cox proportional hazards model, with the use of forward selection based on the likelihood ratio test, will be implemented for multivariate analysis to determine which prognostic factors identified in the univariate analysis, including mitral inflow velocities, DT, IVRT, mitral annular velocities, LA volume, and LA strain were significantly related to clinical events in the follow-up period.

A safety analysis dataset will be used to assess safety and tolerability variables. All patients who received at least one dose of nebivolol or carvedilol, and for whom post-dose data are available, will be included in the safety population. Patients will be censored 7 days after their last dose of study medication. A value of *p* < 0.05 will be considered statistically significant.

Potential attrition bias will be mitigated by conducting dropout analysis and intention-to-treat analysis. Given that dropouts are expected, multiple imputation, based on regression methods, will be performed to complete the data. A fully specified statistical analysis plan will be written before unmasking of the data.

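### The definition of clinical events does not fit the event-free survival analysis: NYHA class has no event date, death is not named, and the 7-day censoring rule does not say which analysis it governs

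*Protocol article*

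**What the plan says.** All references are to the protocol article.

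- **Trial objectives** gives the only definition: "Clinical events are defined as symptom severity (New York Heart Association (NYHA) classification) and hospitalization due to HF".
- **Outcome measurements** makes these events the secondary outcome: "Secondary outcomes include occurrence of clinical events". It continues: "Symptom severity (NYHA classification) and hospitalization will be evaluated at baseline and at maintenance follow-up visits", here without limiting hospitalization to heart failure. On death it says only: "Any complications, discontinuations, and deaths occurring during the study period will be noted".
- **Follow-up protocol** names NYHA and the events as two items: "NYHA functional class and predefined clinical events will be recorded at each clinical visit". Visits are monthly for three months and then every three months to month 12.
- **Statistical analyses**, efficacy paragraph: "Event-free cumulative survival rates will be plotted using the Kaplan-Meier method and comparisons will be made between patients given nebivolol and carvedilol", with a log-rank test and a Cox model for clinical events. The same paragraph prescribes intention-to-treat and analyses patients as randomized "irrespective of whether a SAE occurred before or following discontinuation of study medication".
- **Statistical analyses**, next paragraph, after the safety population is defined: "Patients will be censored 7 days after their last dose of study medication". The sentence that follows sets the significance level for the study as a whole.

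**The concern.** Kaplan-Meier, log-rank and Cox methods need an event that either happens on a date or does not. One of the two named components, symptom class, is an ordinal state present from the first visit. The most serious outcome, death, is not named at all. Someone applying the definition literally would have to invent an NYHA rule and would treat a death without a previous heart failure admission as a censored observation. Such censoring would matter if deaths differed between arms, because the arm with more early deaths would have fewer patients left to be admitted.

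The 7-day sentence adds a second uncertainty. If it were carried into the event-free survival comparison, admissions and deaths after the drug is stopped would drop out, and that comparison would no longer follow the randomized arms for 12 months.

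**Working it through.** The article gives no event rate, hazard ratio, event count or discontinuation rate, so there is no figure for this analysis to reproduce. The check is mainly of the text.

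**1. Sections side by side**

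| Question | Trial objectives | Outcome measurements | Follow-up protocol | Statistical analyses |
|---|---|---|---|---|
| Is NYHA class an event? | Yes | Evaluated as part of the secondary outcome | Listed apart from the events | Not stated |
| Which hospitalizations count? | Heart failure only | Cause not given | Not stated | Not stated |
| Is death an event? | Not named | Noted only | Not named | Not stated; the label event-free survival could include it |

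**2. The definition applied to hypothetical patients**

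- *Class II at baseline and class II throughout.* Read literally, the patient has a symptom class from day 0. No threshold says whether this is an event.
- *Class II, then III, then II again.* No rule says whether the worsening counts or on which date. With three-monthly visits the date is known only to within three months. Blinded reading is stated only for the echocardiographic images, so the grade is given in an open-label setting.
- *Admission for a cause other than heart failure.* Not an event under Trial objectives; open under Outcome measurements.
- *Death without a previous heart failure admission.* Not an event under the stated definition, so censored by default.
- *Heart failure admission more than 7 days after the last dose.* Counted under the efficacy paragraph; lost only if the 7-day sentence is applied to this analysis.

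**3. Scale of the analysis affected**

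Statistical analyses describes no time-to-event methods other than Kaplan-Meier, log-rank and Cox. For a 1:1 log-rank test at two-sided 5 %, with an assumed hazard ratio of 0.5 (not in the documents):

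- Events for 80 % power: 4 × (1.960 + 0.842)² / (ln 0.5)² = 31.4 / 0.480 = 65.4, so 66, which is more than the 62 patients.
- Power with d events: Φ(0.693 × √d / 2 − 1.960), which gives 19 % for d = 10, 34 % for d = 20 and 48 % for d = 30.

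This agrees with the protocol's own statement under Sample size that secondary outcomes are likely to be underpowered.

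**4. The primary analysis**

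The sample size uses only E/E' (difference 5.0, SD 5.0, power 90 %, two-sided 5 %): 2 × (1.960 + 1.282)² × 5.0² / 5.0² = 21.02, so 22 per arm, and 22 / 0.70 = 31.4 against the stated 31. No event assumption enters it.

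**The case against.** The strongest reply has four parts.

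- **This is a journal article that promises a full analysis plan.** NYHA thresholds and censoring details could sit there. That would answer a charge of missing detail. It does not answer a definition that is stated and does not fit the analysis stated with it, or sections that differ from one another.
- **The text may be loose rather than wrong.** Follow-up protocol separates NYHA from the events, and hospitalization in Outcome measurements may be shorthand for the definition already given. Event-free survival may have been meant to include death. All of this is possible. A reader might infer that the protocol sets out to censor deaths; it says no such thing. But if death was meant, the definition under Trial objectives omits it, so the wording needs correcting on either reading.
- **The 7-day rule belongs to safety.** This largely stands. A reader might infer that it contradicts intention-to-treat outright. It sits in the safety paragraph, and an on-treatment window for safety does not conflict with intention-to-treat for efficacy. What remains is that the sentence names no analysis and is followed by one that applies to the whole study. The reasons given for reducing, interrupting or ending treatment or participation are side effects, hypotension, bradycardia and detriment to wellbeing. Informative censoring is therefore plausible, but the documents do not establish it.
- **The size cannot be shown.** This stands. It is tempting to take 62 × 0.30 = 18.6, about 19 patients, as those whose later events the 7-day rule could remove. The 30 % is follow-up loss, not drug discontinuation, and patients lost to follow-up have no later events recorded under any rule.

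**Conclusion.** The point holds as a mismatch between a stated definition and a stated analysis. The NYHA component cannot be used as a dated event, death is outside the definition, the sections differ on NYHA and on the type of hospitalization, and the scope of the 7-day rule should be written down. That deaths would be censored follows by default from the definition and is not stated. A conflict with intention-to-treat arises only if the 7-day rule is applied to the event-free survival comparison. No count of lost or miscoded events can be given. The consequence is confined to a secondary analysis of low power, so this should be corrected but does not threaten the main result. Low power does not make the definition unimportant: with few events, recoding a handful could change the apparent direction.

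**What to change.** Before the data are unmasked, amend the text as follows.

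1. Define the time-to-event outcome as first heart failure hospitalization or death from any cause, from randomization to 12 months, regardless of whether study drug is still taken. If heart failure hospitalization alone is wanted, death has to be handled explicitly as a competing event.
2. Take NYHA class out of the event definition and analyse it separately as an ordinal outcome at 12 months, adjusted for baseline class.
3. Use one definition of hospitalization in Trial objectives, Outcome measurements, Follow-up protocol and Statistical analyses.
4. State that censoring 7 days after the last dose applies only to an on-treatment safety summary, and show serious adverse events and deaths for the full 12 months beside it.

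**Cost:** wording only. Deaths, hospitalizations and NYHA class are already recorded. Patients who stop the drug but stay in the trial must be followed for events to month 12, which the intention-to-treat wording already implies. The drawback is that events after stopping are harder to attribute to the drug; the on-treatment summary covers that.

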## Methods/design

### Ethics

This study follows the principles set forth in the Helsinki Declaration, meaning that all patients sign a written informed consent stating that participation is voluntary and that participation can be withdrawn at any time, without any negative consequences concerning their current or future medical treatment. The study protocol (version #1, 7 October 2015), which follows the Standard Protocol Items: Recommendations for Interventional Trials (SPIRIT) guidelines (see Additional file 1), has been approved by the Institutional Review Board of Dong-A University Hospital.

### Patient population

This study will take place at Dong-A University Hospital. Patients will be eligible for the study if they have a left ventricular ejection fraction (LVEF) ≥40 %, NYHA functional classes I, II or III status, and have been clinically stable without hospital admission for HF in the preceding 3 months. Men and women over 70 years of age are eligible (Table 1). In the present study, preserved LVEF is defined as an EF ≥40 % using a modified Simpson’s rule [10]. Pharmacological therapy other than that with the study drug, including ACE and statin use, is allowed at the discretion of the attending physician. Patients who have contraindications to the study drug or major concomitant diseases are to be excluded (Table 1).

**Table 1 Tab1:** Eligibility criteria

**Inclusion criteria** Subjects > 70 years of age Either gender First diagnosis of heart failure defined as: a) Mild or moderate symptomatic heart failure (NYHA calss I to III) b) An echocardiographic left ventricular ejection fraction ≥ 40% Patients who provide written informed consent
**Exclusion criteria** History and/or clinical documentation of pulmonary embolism Severe heart failure (NYHA IV or need for inotropic support) Primary valvular heart disease Pericardial disease Severe obstructive lung disease Primary pulmonary hypertension Occupational lung disease Asthma Severe renal failure (serum creatinine >2.0 mg/dL) Significant peripheral vascular disease Severe bradycardia (heart rate< 50 beats/minutes) Second or third-degree atrio-ventricular block Atrial fibrillation Life expectancy < 1 year Concern for inability of the patient to comply with study procedures and/or follow up Any condition which in the opinion of the Investigator would make it unsafe or unsuitable for the patient to participate in this study Involvement in the planning and/or conduct of the study Participation in another clinical study with an investigational product during the preceding 30 days Unable to give informed consent

### Study design

This study is a prospective, randomized, open-label, single-centre, active controlled study with two parallel study groups. The choice of a prospective and open-label study was felt to be a reasonable reflection of clinical practice in only one center with a small sample. The randomized design was adopted to minimize bias in this single-center study. The dose of nebivolol was chosen on the basis of the SENIORS study [6]. The control arm will receive carvedilol because it is the β-Blocker that is indicated for the broadest population and is the most frequently used β-Blocker worldwide. A treatment duration of a minimum of 12 months was selected as a result of the SENIORS trial. The overall study design is depicted in Fig. 1.

**Fig. 1 Fig1:**
[figure not shown]
Overall algorithm of the study

### Randomization

All new patients admitted to the Dong-A University Cardiology Department will be screened for participation eligibility in the study by the principal investigator. Randomization following initial echocardiographic testing can be performed immediately after enrollment for patients who fulfill all the eligibility requirements. Patients will be randomly allocated to one of two conditions: (1) nebivolol treatment (10 mg once daily) or (2) carvedilol treatment (25 mg twice daily). Enrollment is expected to continue for approximately 12 months. Random treatment assignments will be generated using Excel spreadsheet software (Microsoft Corporation, Redmont, DC, USA). Eligible patients will be randomly assigned in a 1:1 ratio to receive either nebivolol or carvedilol. Randomization will be performed by an individual not involved in the study and will be kept concealed. Following randomization, the first dose of study medication will be administered to the patient as soon as possible. Potential attrition bias will be mitigated by only including patients who are motivated to recieve treatment. We will take efforts to minimize dropout and any potential biases attributable to dropout will be explored statistically. If a participant wishes to withdraw from the study, the reason for withdrawal will be documented in the participant’s records for the subsequent analysis in the interpretation of the results.

### Outcome measurements

The primary efficacy variables are mitral inflow velocities (E and A waves), deceleration time of the E wave (DT), isovolumetric relaxation time (IVRT), mitral annular velocities (early diastolic velocity of mitral annulus (Ea) and late diastolic velocity of mitral annulus (Aa) waves), left atrial (LA) volume, and LA strain (global systolic and diastolic LA strain), which will be measured via echocardiographic evaluation after 12 months of treatment. Mitral E/A and E/Ea ratios will be calculated. Parameters from Doppler analysis, M-mode echocardiography, and 2D-transthoracic echocardiography will be used. All echocardiographic images will be interpreted by an observer who is blinded to clinical data.

Secondary outcomes include occurrence of clinical events. Symptom severity (NYHA classification) and hospitalization will be evaluated at baseline and at maintenance follow-up visits. Vital signs, including heart rate and blood pressure, will be measured at every visit. Any complications, discontinuations, and deaths occurring during the study period will be noted. Each patient’s medical history and the results of a clinical examination will be recorded at baseline by the attending physician.

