### Sample size

Calculation of sample size was done based on the primary outcomes and the primary analysis for the intention-to-treat population. The sample size was calculated using the study’s primary objective, to detect a difference in E/E’ of 5.0 between nebivolol and carvedilol treatment with a power of 90 %. On the basis of previous reports, we assume the standard deviation of E/E’ to be approximately 5.0 in both treatment groups [11, 12]. We adjusted the sample size for an estimated follow-up loss rate of 30 %, a two-sided level of significance *a* = 5 % and a power of 1 − β = 90 %. Thirty-one patients in each group are required to detect statistical differences with a two-sided Student’s *t* test given these parameters. Therefore, a total of 62 patients will be included in the analysis. The statistical analyses will be performed on the full dataset, which will include data from all randomized patients receiving at least one dose of study medication. Patients who are judged to be ineligible after study registration will be excluded from the analysis. Given the sample size, this study is likely to be underpowered in terms of assessing secondary outcomes.

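### Nine echo measures are named primary, the trial is sized on E/E’, which is not expressly among them, and the analysis section leaves the primary outcome unnamed with no multiplicity rule.

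*Protocol article*

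**What the plan says.** Three sections of the protocol article bear on the primary endpoint.

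- **Outcome measurements.** The list opens "The primary efficacy variables are mitral inflow velocities (E and A waves), deceleration time of the E wave (DT), isovolumetric relaxation time (IVRT"), continues with the mitral annular velocities Ea and Aa, and ends with "left atrial (LA) volume, and LA strain (global systolic and diastolic LA strain), which will be measured via echocardiographic evaluation after 12 months of treatment". That makes nine measures: E, A, DT, IVRT, Ea, Aa, left atrial (LA) volume, systolic LA strain and diastolic LA strain. A separate sentence adds "Mitral E/A and E/Ea ratios will be calculated", without calling either ratio primary.
- **Sample size.** The calculation is made "to detect a difference in E/E’ of 5.0 between nebivolol and carvedilol treatment with a power of 90" per cent, and "we assume the standard deviation of E/E’ to be approximately 5.0 in both treatment groups". The two-sided 5 % is not divided. With 30 % loss to follow-up this gives 31 per group, 62 in total. No other measure is sized.
- **Statistical analyses.** A primary outcome, in the singular and unnamed, is compared between arms. Other echo indices are tested separately at 12 months. The null hypothesis concerns change in diastolic function as a whole, not one variable. The threshold is p "< 0.05 will be considered statistically significant". There is no hierarchy, no split of alpha and no rule for how many measures must succeed. The section adds: "A fully specified statistical analysis plan will be written before unmasking of the data".

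**The concern.** The three sections cannot all be followed. The variable that carries the sample size appears in the outcomes section only as a derived ratio, and none of the nine variables called primary has a sample size behind it. A reader of the results could not tell from the protocol whether the trial succeeds on E/E’, on any of the nine, or on some combination.

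What is at stake is the meaning of the stated 5 % error rate and 90 % power. Both were derived for one test of one variable. If a significant result on any listed measure could be reported as meeting the primary objective, the error rate is several times the stated one. If multiplicity were then controlled at 5 % over the list, the power would fall well short of 90 %.

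**Working it through.** **Inputs from the protocol article.** Difference in E/E’ 5.0, SD 5.0, two-sided alpha 0.05, power 90 %, loss 30 %, 31 per group (Sample size); nine measures named primary, eleven if the two ratios are added (Outcome measurements); p < 0.05 for each test (Statistical analyses).

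**Inputs assumed.** No success rule is stated, so the error rates below assume that any one significant measure suffices. No correlations between measures are given, so a range is shown.

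**1. The plan's own figure.** Standardised difference d = 5.0/5.0 = 1. Normal approximation: n = 2 × (1.960 + 1.282)² / 1² = 21.01, rounded up to 22 per arm. The t-test solution is 22.02. Allowing for loss: 22/0.70 = 31.4, or 22.02/0.70 = 31.5. The stated 31 per group is reproduced within rounding, for E/E’ alone at an undivided 5 %.

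**2. Reading A: the unnamed primary outcome is E/E’.** There is one test at 5 %. With 31 × 0.70 = 21.7 evaluable per arm, t-test power at d = 1 is 0.896. The stated error rate and power hold, and it is the list in Outcome measurements that is wrong.

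**3. Reading B: every listed measure is primary and any one suffices.** For k independent tests with no true difference:

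- Either direction: 1 − 0.95^k, which is 1 − 0.95^9 = 0.370 and 1 − 0.95^11 = 0.431.
- Favouring nebivolol: 1 − 0.975^k, which is 1 − 0.975^9 = 0.204 and 1 − 0.975^11 = 0.243.

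With equal pairwise correlation (simulation, 400,000 replicates):

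| Assumed correlation | Either direction, k = 9 | Either direction, k = 11 | Favouring nebivolol, k = 9 | Favouring nebivolol, k = 11 |
|---|---|---|---|---|
| 0 | 37 % | 43 % | 20 % | 24 % |
| 0.3 | 33 % | 38 % | 17 % | 19 % |
| 0.5 | 27 % | 30 % | 14 % | 15 % |
| 0.7 | 20 % | 22 % | 10 % | 11 % |
| 0.9 | 12 % | 13 % | 6 % | 7 % |
| Nominal, one test | 5 % | 5 % | 2.5 % | 2.5 % |

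E, A and Ea also enter the ratios, so independence of all eleven is an upper reference. A simulation with nine independent raw measures and the two ratios built from them gave about 39-40 % in either direction.

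**4. Cost of controlling error under reading B.** With Bonferroni, alpha per test is 0.05/9 = 0.00556 or 0.05/11 = 0.00455. At 21.7 evaluable per arm and d = 1, t-test power for E/E’ falls from 0.896 to 0.643 (k = 9) or 0.616 (k = 11). To regain 90 % by the normal approximation, 33 or 34 evaluable per arm are needed: 33/0.70 = 47.1, so 48, and 34/0.70 = 48.6, so 49. That is 96 or 98 patients in total instead of 62.

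**The case against.** The strongest reply is that the Sample size section ties the primary objective to E/E’, and that the Statistical analyses section separates a single primary outcome from the other indices. Read together, these make E/E’ the natural primary endpoint and the rest supportive. No sentence says that one significant index meets the objective, and a fully specified analysis plan is promised. This largely stands: reading A is plausible, and under it the error rate and power are as stated. It does not remove the contradiction. The analysis section never names E/E’, and the outcomes section gives a different list under the label primary. A later plan would have to overrule one of these sections.

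Three stronger readings are tempting, and the article does not support them.

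- *Eleven measures are called primary.* Nine are. The two ratios stand in a separate sentence without that label, and the sized variable is one of them.
- *A false claim of superiority is likely.* Even with eleven independent tests and any one sufficing, the chance of a false positive is 43 % in either direction and 24 % in nebivolol's favour. The risk is inflated, but it stays below one half.
- *Because the trial is open-label and the principal investigator holds the final dataset, the promised analysis plan offers no protection.* The article does not say that results by arm are viewed before the plan is written, and echo images are read by an observer blinded to clinical data. Blinded reading limits measurement bias; it does not settle which measure is primary.

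**Conclusion.** The point holds as a contradiction between three sections: nine measures are named primary, a variable not expressly among them is sized, and the analysis section leaves the primary outcome unnamed with no multiplicity rule.

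Its size depends on the reading. If E/E’ is the sole primary, the 5 % and 90 % hold and the defect is the wrong list. If all listed measures are primary and any one suffices, the chance of a false positive is 37-43 % under independence and about 20-30 % at correlations of 0.5-0.7; in nebivolol's favour it is 20-24 % and about 10-15 %, against a nominal 2.5 %. Bonferroni control would cut power for the 5-point E/E’ difference from about 90 % to about 62-64 %. The any-one rule and the correlations are assumptions, not statements of the article. The choice of primary endpoint governs the trial's main claim, so it should be settled in the protocol text.

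**What to change.** In Outcome measurements and in Statistical analyses, name E/E’ (E/Ea, with one notation throughout) at 12 months, adjusted for baseline, as the single primary endpoint. It is the variable already sized, and regression adjusted for baseline is already among the stated analyses. List the nine measures now called primary, together with E/A, as secondary or exploratory, reported with estimates and confidence intervals and with no claim of success on the primary objective.

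The cost is wording only: the sample size stays at 62 and no measurement is added. The downside is that a positive result on another echo index can no longer be called primary.
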